### Outcomes

All outcome measures and assessment time points for patients are listed in Table
2.

**Table 2 T2:** Outcome measures, assessments, and frequency and scope of study visits

**Visit**	**Screening**	**Instruction** **(Videotherapy and Non-Video Group)**	**Baseline**	**Training phase**	**End of Training**	**Follow-up**
**Time**	Week 1: Day 1-3	Week 1: Day 4-5	Week 2	Week 2 – 7 + 4 days	Week 8 + 4 days	Week 31 + 1 week

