### Interventions

One experimental and two control groups will be built. All patients of all groups will conduct their individual rehabilitational programme as prescribed by their respective neurologist beside participation in our scheme. The standard rehabilitational programs will not be limited in their amount to allow participation to our study but must not be experimental or part of another clinical trial.

The respective intervention starts with a practice at the site during the last week at their inpatient stay. Patients will be asked to start immediately with the self-administered treatment after their return back home. All patients will keep record of their training in a pre-printed diary and will receive a weekly phone call in which compliance of the patients will be monitored.

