**Preparation of patient**						
**Instruction and training**		X				

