**Primary efficacy endpoint**						
**Wolf Motor Function Test**			X		X	X

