#### Primary endpoint

The primary efficacy endpoint is the change in scores of the WMFT
[16] between baseline and after six weeks of rehabilitation treatment between the videotherapy group, the standard and videotherapy group and the non-video group.

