### Randomization: implementation

The allocation of patients will be conducted by an investigator without any clinical involvement in the trial using proper random sequences unbeknown to the patients or study team: The randomization and further allocation is performed centrally via fax at the Institute of Medical Biometry and Statistics at the University Hospital Schleswig-Holstein, Campus Lübeck, Germany (IMBS) after the respective investigator had screened the respective patient and obtained his/her written informed consent.

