### Statistical analysis

#### Study population

According to the "ICH Topic E 9" there are two different sets (intention to treat set and per protocol set) for the statistical analysis.

The primary analysis will be based on the intention to treat population where missing values will be imputed with a mean imputation. Similar rates of missing baseline observations between the treatment groups as well as analogous results from sensitivity analyses will be used to support the interpretation. As sensitivity analyses, the imputation methods "Last Observation Carried Forward" principle and best or worst case imputation will be applied.

A secondary analysis will be based on the per protocol population. Here we consider only patients which complete at least 66,67% of the training sessions. This value is derived from the pilot study
[10], where significant treatment effects occurred after duration of 20 training days. The analyses will be the same as with the intention to treat.

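### The baseline WMFT of the primary change score is taken after allocation and after arm-specific practice, which mainly exposes videotherapy versus standard

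*Protocol article*

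**What the plan says.** Under Primary endpoint: "The primary efficacy endpoint is the change in scores of the WMFT", measured from baseline to the end of six weeks of treatment.

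Table 2 (Outcomes) gives the visit order:

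- Screening: Week 1, Day 1-3.
- Instruction: Week 1, Day 4-5, with the column restricted to the "Videotherapy and Non-Video Group". Its single entry is "Instruction and training".
- Baseline: Week 2. The row "Wolf Motor Function Test" has its first mark here and none at Screening or Instruction.
- Training phase: Week 2 to 7, followed by End of Training in Week 8.

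The Interventions section says: "The respective intervention starts with a practice at the site during the last week at their inpatient stay". It continues: "Patients will be asked to start immediately with the self-administered treatment after their return back home".

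Randomization: implementation says that allocation takes place centrally by fax "after the respective investigator had screened the respective patient and obtained his/her written informed consent". No baseline efficacy test is named as a precondition.

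Trial design calls the study open. Blinding says that patients can be blinded between videotherapy and non-video, but not against standard.

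**The concern.** A change score protects a randomised comparison only if its baseline cannot be influenced by allocation. Here two of the three arms receive their own instruction and practice before the baseline WMFT, and the third does not. Any shift that this produces in the baseline passes point for point into the difference in change scores.

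Two mechanisms are possible. Practice before baseline could raise the baseline in the training arms, so that part of the treatment gain is subtracted from the measured effect. Knowledge of allocation in an open trial could move baseline performance or its rating either way.

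The comparison most at stake is videotherapy versus standard. It is the first in the hierarchy, it is the one on which the sample size rests, and the standard group has no instruction visit.

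**Working it through.** **1. Order of events.** The article does not date randomisation, so its place has to be inferred. Randomisation follows screening and consent, and screening is Week 1, Day 1-3. A visit held for two named arms on Day 4-5 requires that allocation be known by then. The first WMFT is in Week 2. The order is therefore screening, allocation, arm-specific practice, baseline WMFT. No section of the article places a WMFT before allocation.

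**2. The plan's own sample size.** Inputs from Sample size and Table 3: difference 2.5 points, standardised effect 0.5 (so SD = 2.5/0.5 = 5), alpha 0.035 (two-sided, since the alternative is stated as unequal to one half), power 90%, dropout 20%, Mann-Whitney test.

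- Noether's formula: P(X>Y) = Φ(0.5/√2) = 0.638. Total N = (2.108 + 1.282)² / (12 × 0.25 × 0.138²) ≈ 200.7, or 100.3 per arm. Dividing by 0.8 gives 126 after rounding up.
- Two-sample normal formula: 92 per arm. Multiplying by π/3 for the Mann-Whitney test gives 97, and dividing by 0.8 gives 122.

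Both lie close to the stated 125 per group, which leaves 125 × 0.8 = 100 evaluable. The illustration below uses this base.

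**3. Illustration: videotherapy baseline raised relative to standard.** The size of the shift, b, is an assumption.

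Power = Φ(d × √(n/2 × 3/π) − z), with n = 100, z = 2.108 for alpha 0.035, and d = (2.5 − b)/5. The root equals √47.75 = 6.910.

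| Assumed shift b (points) | Measured difference | d | Power |
|---|---|---|---|
| 0 | 2.50 | 0.500 | 91% |
| 0.17 | 2.33 | 0.467 | 87% |
| 0.5 | 2.00 | 0.400 | 74% |
| 1.0 | 1.50 | 0.300 | 49% |

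The value 0.17 comes from assuming that gains are proportional to days. Six weeks of five working days are 30 sessions, two instruction days are 2/30 of that, and 2/30 × 2.5 = 0.17.

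**4. Illustration: no true effect, videotherapy baseline lowered relative to standard.** The two-sided rejection rate is 1 − Φ(2.108 − 6.910 × b/5) + Φ(−2.108 − 6.910 × b/5).

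- b = 0.5: 0.078 + 0.003 = 0.081, about 8%.
- b = 1.0: 0.2338 + 0.0002 = 0.234, about 23%.

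Without a shift the rate is 3.5%.

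**5. The two primary comparisons.** Standard has no instruction visit, and its patients cannot be blinded against videotherapy, so a shift in the videotherapy arm has no counterpart there. The non-video group attends the same visit, uses equivalent material apart from the slideshows, and can be blinded against videotherapy. Shifts in that comparison should largely cancel, although each arm practises its own condition.

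**The case against.** The strongest reply is that the order of visits may do little harm. Table 2 lists the visit as preparation of the patient, it lasts two days at most, and six weeks of training follow. If gains are proportional to days, the shift is about 0.17 point and power falls only to about 87%. Practice also works against videotherapy, so for a superiority claim it is conservative. This stands as far as it goes: larger shifts are assumed, and the false-positive figures need a lowered videotherapy baseline, which practice would not produce. It does not remove the problem, because knowledge of allocation can act in either direction and the documents do not rule it out.

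Several stronger readings are tempting but not supported:

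- A reader might infer from the analysis section's remark "Similar rates of missing baseline observations between the treatment groups" that the plan itself concedes a post-randomisation baseline. It does not. Baselines can be missing under any visit order, and the remark says only that similar rates would support interpretation.
- A reader might infer that home training has begun before the baseline WMFT, since both carry the label Week 2 and patients start at once on returning home. Overlap is possible but not shown: the Baseline column precedes the Training phase, and the table resolves only to weeks.
- A reader might object that such a baseline is no valid covariate. The primary test is an unadjusted Mann-Whitney test on change scores, so the point does not arise.
- A reader might say that a missing baseline makes the endpoint uncomputable. The plan specifies imputation and sensitivity analyses.

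**Conclusion.** The point holds on the order of visits. The primary endpoint's baseline is measured after allocation and after arm-specific practice, in an open trial. The date of randomisation is inferred, but a visit restricted to two arms makes the inference firm. The Blinding section acknowledges expectation and training intensity as possible influences, but not this one.

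The weight falls on videotherapy versus standard and is much smaller for videotherapy versus non-video. Neither the direction nor the size of the bias can be taken from the documents. The power figures (91% falling to 87%, 74% or 49%) and false-positive figures (3.5% rising to about 8% or 23%) illustrate assumed shifts, with SD 5 and 100 evaluable per arm. They are not estimates of what will happen. The point merits correction because a baseline already influenced by allocation cannot be reliably repaired in the analysis, whereas the remedy is simple.

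**What to change.** In Table 2, move the baseline WMFT, together with the Frenchay Arm Test, Stroke Impact Scale, Motor Activity Log and Box and Block Test, to the end of the Screening visit. They should follow confirmation of eligibility and precede the randomisation fax and any arm-specific instruction. State in Randomization: implementation that these tests must be complete before the fax is sent. Define change as End of Training minus this pre-randomisation value. The Barthel Index and Modified Rankin Scale are already recorded at Screening and can be used in the same way.

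The sample size of 125 per group and the planned tests stay as they are. The cost is a longer pre-randomisation visit, on top of an already full set of screening tests. Placing the scales after the eligibility check spares screening failures the extra battery. The change score will also contain a few more days of natural recovery, equal across arms. The change does not address expectation effects at End of Training, which remain a limitation of the comparison with standard.

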**Screening, supervision**						
**Informed consent**	X					
**Inclusion/exclusion criteria**	X					
**Background medical history**	X					
**Concomitant medication**	X					
**Screening**	X					
**Beck Depression Inventory**	X		X	X (week 5)	X	X
**Amount of training with videotherapy DVDs**						X
**Preparation of patient**						
**Instruction and training**		X				
**Primary efficacy endpoint**						
**Wolf Motor Function Test**			X		X	X
**Secondary efficacy endpoint**						
**Frenchay Arm Test**			X		X	X
**Stroke Impact Scale**			X		X	X
**Barthel-Index**	X		X	X (week 5)	X	X
**Modified Rankin Scale**	X		X		X	X
**Motor Activity Log**			X	X (week 5)	X	X
**Box and Block Test**			X		X	X
**Further treatment**						
**Telephone calls**				Weekly		
**Diary**				Daily by the patient		

#### Primary endpoint

The primary efficacy endpoint is the change in scores of the WMFT
[16] between baseline and after six weeks of rehabilitation treatment between the videotherapy group, the standard and videotherapy group and the non-video group.

#### Secondary endpoints

The secondary endpoints concern quality of life related to improvement in motor function indices (tested via FAT, 17) and autonomy (tested via SIS
[18], Barthel-Index - BI
[24], Modified Rankin Scale - MRS
[25], Motor Activity Log – MAL
[26], Box and Block Test - BBT
[27]). A secondary endpoint is the change in the WMFT
[16] scores between baseline and after end of the treatment compared to the non-video and standard groups. The changes in the scores and mortality between all groups at all time points will be tested pairwise. Furthermore, the difference between the end of treatment and 6 month after the training will be investigated within each group.

#### Subgroup analysis

We will perform pairwise comparisons between all groups (videotherapy, non-video and standard) in dependency of the following variables: center, age, gender, race, dominance of the affected hemisphere, affected hemisphere, type and amount of additional physio- and/or occupational or other therapeutic treatments during training phase, chronicity/sub-chronicity of stroke symptoms. Chronicity is defined by manifestation of stroke related motor symptoms ≥ 6 months after the incident.

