## Methods/design

### Trial design

The form of our clinical study will be: multicenter, open, randomized, placebo-controlled, paralleled group trial with three investigative arms conducted in Germany (5 sites). This study aims at demonstrating superiority of the videotherapy over both physical training and standardized physical therapeutic treatments. We will use equal number of patients for the randomization on the three groups (1:1:1).

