The multicenter study will take place at 5 sites in Germany: Department of Neurology of University of Leipzig, Department of Neurology of Brandenburg Klinik Bernau near Berlin, Clinic for Neurology of at Campus Lübeck University Medical Center Schleswig-Holstein, St. Mauritius Therapieklinik at Meerbusch near Düsseldorf, and the Neurological Centre of Segeberger Kliniken GmbH at Bad Segeberg. All sites represent the main venues for stroke patients and stroke-related rehabilitation in their surrounding areas, thus able to reach the expected sample size of stroke patients. Because the study centers at Lübeck and Leipzig do not provide treatment for patients in their post-stroke rehabilitation phase, these sites will recruit patients from nearby rehabilitation centers to where their sub-acute patients have been referred further on. Recruited patients therefore will have been pre-screened at the respective site and will be invited at the end of their rehabilitative treatment to the trial site for participation. All recruitment formalities and ambulatory or stationary assessments will be conducted in the sites stated above with patients transported to the respective clinics.

Patients' data will be assessed in the respective sites. Data management and monitoring of the trial sites will be conducted by the Center for Clinical Trials, University of Lübeck. Biostatistical analysis and randomization will be performed by the Institute of Medical Biometry and Statistics, University of Lübeck. An independent Data and Safety Monitoring Board (DSMB) of two clinicians and a biostatistician will to supervise patients' safety, as well as statistical analysis and interpretation.

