### Sample size

The calculation of the sample size is based on the aim to detect a difference of 2.5 points in the WMFT
[16] between the videotherapy- and the standard group concerning the change from baseline until the end of rehabilitation, corresponding to δ = 0.5, with a power of 90% in the final of two analyses. The critical difference of 2.5 points in the WMFT
[16] results from our pilot study
[10-13]. Allowing for a maximal drop out of 20% of the patients, 125 patients need to be included in the study for each group, rendering a total sample size of 375 (α_2_(1) = 0.035, Mann–Whitney test).

The interim analysis is conducted according to Wang and Tsiatis
[34], after half of the patients in each group (63 in each group, a total of 188) have concluded the rehabilitation program. If the effect is considerably greater than assumed (δ = 0.7, corresponding to a difference of 3.5 change points), there is a probability of 80% to detect this at this early stage and hence to terminate the study early.

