#### Subgroups

In the subgroup analyses the results of the test inventories and assessments stated above are used.

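### Subgroups are planned as pairwise arm comparisons with no interaction estimate, and one listed subgroup variable is measured after randomisation

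*Protocol article*

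**What the plan says.** The section Subgroup analysis (under Outcomes) reads: "We will perform pairwise comparisons between all groups (videotherapy, non-video and standard) in dependency of the following variables: center, age, gender, race". The list continues with "dominance of the affected hemisphere, affected hemisphere, type and amount of additional physio- and/or occupational or other therapeutic treatments during training phase" and ends with chronic versus sub-chronic symptoms, divided at six months. That makes eight items if type and amount of additional therapy count as one.

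The section Subgroups (under Statistical analysis) adds one sentence: "In the subgroup analyses the results of the test inventories and assessments stated above are used". It gives no test, level, cut-point or rule for reading the results.

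For comparisons between arms, the sections on the primary and secondary endpoints name the exact Mann-Whitney test and, for mortality, the Chi-squared test. Both compare two groups. An interaction or heterogeneity test is mentioned nowhere. The secondary endpoints are called exploratory; the subgroup analyses carry no such label.

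**The concern.** A subgroup analysis asks whether the treatment effect depends on a patient characteristic. A two-group test repeated within each level asks something else, namely whether the effect can be detected in that level with the patients who fall there. The answer mixes effect size with subgroup size. An effect that is identical in all patients will then often be significant in one level and not in the other, and a reader may take that as evidence of a difference.

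The hemisphere items show what is at stake. The Background reports publications in which mental techniques helped only after left-hemispheric stroke, and it disputes them with imaging data from eight right- and eight left-hemispheric patients. Affected hemisphere is on the subgroup list. A one-sided pattern produced by small numbers alone could be read into that dispute.

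A second fault lies in the list itself. Therapy received during the training phase is known only after allocation and may be affected by it. Patients in the standard arm know that they receive no trial treatment, and the Interventions section leaves the amount of usual rehabilitation unlimited. Comparing arms among patients with, say, much additional therapy conditions on something that allocation may have changed.

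**Working it through.** **Inputs from the article.** Sample size section: "corresponding to δ = 0.5, with a power of 90% in the final of two analyses"; "α_2_(1) = 0.035, Mann–Whitney test"; "Allowing for a maximal drop out of 20% of the patients, 125 patients need to be included in the study for each group". The alternatives are two-sided (Primary endpoint, Statistical analysis). Allocation is 1:1:1, at five sites.

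**Inputs assumed.** The article gives no subgroup proportions and no level for subgroup tests. I use splits from 50:50 to 80:20, equal across arms, and levels of 0.05 (stated for the secondary pairwise tests) and 0.035. The number per arm is 100 (125 × 0.8) or 125, the latter because the intention-to-treat analysis imputes missing values. Data are taken as normal, with an identical effect of 0.5 SD in every subgroup.

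**Step 1: reproduce the planned sample size.** Noether's formula for the Mann-Whitney test, with P = Φ(0.5/√2) = 0.638:

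n per group = (2.108 + 1.282)² / [2 × 12 × 0.25 × (0.638 − 0.5)²] = 100.3 (unrounded P), and 100.3 / 0.8 = 125.4.

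The stated 125 reproduces, so δ = 0.5 and 100 evaluable per arm are the plan's own working values.

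**Step 2: power within a subgroup of n per arm.** Power = Φ(δ × √(n × (3/π)/2) − z), where 3/π is the efficiency of the Mann-Whitney test relative to the t-test for normal data. With n = 50 at 0.05: Φ(0.5 × √(47.75/2) − 1.960) = Φ(0.483) = 0.685.

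**Step 3: probability that exactly one of two levels is significant.** This is p1(1 − p2) + p2(1 − p1). For 50:50 it is 2 × 0.685 × 0.315 = 0.431. For 80:20 (80 and 20 per arm) it is 0.871 × 0.661 + 0.339 × 0.129 = 0.619.

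| Level | Per arm | 50:50 | 70:30 | 80:20 |
|---|---|---|---|---|
| 0.05 | 100 | 43.1% | 51.7% | 61.9% |
| 0.05 | 125 | 34.3% | 45.1% | 58.0% |
| 0.035 | 100 | 46.6% | 54.8% | 64.4% |
| 0.035 | 125 | 39.1% | 49.8% | 62.2% |

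Simulated Mann-Whitney tests (20,000 runs, 100 per arm, level 0.05) gave 43.6% for 50:50 and 53.0% for 70:30.

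**Step 4: centres.** With five equal centres of 20 per arm, power per centre is 0.339. The centres give mixed results with probability 1 − 0.339⁵ − 0.661⁵ = 0.87. Equal centres are an assumption.

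**Step 5: the interaction test.** Under a uniform effect, an interaction test at 0.05 signals a difference in 5% of trials by construction, for one variable and one pair of arms. Its power is low. For a difference in effect of 0.5 at a 50:50 split with 100 per arm, the standard error is √(2 × 2/(50 × 3/π)) = 0.289, and power is Φ(0.5/0.289 − 1.960) = 0.41.

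**Step 6: number of tests.** Five centres plus seven items at two levels each make 19 subgroups. With three arm pairs that is 57 tests per outcome, or 57 × 0.05 = 2.9 expected false positives if there is no effect at all. Eight interaction tests for each of three pairs would give 24 × 0.05 = 1.2, so multiplicity is reduced but not removed.

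**The case against.** The strongest reply is that the article does not say the tests are run within levels. Its wording can be read as comparing arms as a function of each variable, which a model with an interaction term would also satisfy. A fuller protocol or SAP could add such a term without contradicting the article. This stands in part: a reader might infer that interaction tests are ruled out, and the text does not support that. It does commit to pairwise arm comparisons, though, and every between-group test it names is a two-group test, so separate tests by level are the natural reading. That is a method fixed badly, not just a detail left out.

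A reader might also infer that the plan will declare subgroup effects from one significant and one non-significant result, or that subgroup results will decide who receives the DVD. Neither is stated. There is no rule for claiming subgroup effects, neither trial hypothesis concerns a subgroup, and both control groups receive the treatment disk after the training phase. The article also does not say that this trial is meant to settle the hemisphere question. For the comparisons it does specify, it asks for Hodges-Lehmann confidence intervals, so it does not rely on p-values alone.

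On additional therapy, the exclusion criteria bar patients with a planned start of interfering rehabilitation within eight weeks of recruitment. That narrows the problem but does not close it, because usual rehabilitation continues without limit and its amount can still differ by arm.

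**Conclusion.** The point holds as a weakness in the stated subgroup method. On the natural reading, a uniform effect would appear to work in one level and not in the other in about 34% to 64% of trials for a two-level variable, against about 5% false signals with an interaction test at 0.05. The range rests on an effect of 0.5 SD and 100 to 125 patients per arm, both from the article, and on assumed splits of 50:50 to 80:20 and levels of 0.035 to 0.05. Smaller splits or other levels would move it.

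The fault with additional therapy needs no arithmetic. It is a post-randomisation variable, and arm comparisons within its levels lose the protection of randomisation.

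The sample size, the primary hypotheses and their error control are not affected. What is at risk is how the subgroup results are read.

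**What to change.** In the sections Subgroup analysis and Subgroups:

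- For each baseline variable, report the treatment effect in each level with a 95% CI, and a treatment-by-subgroup interaction estimate with its 95% CI. A rank-based or proportional-odds model of the Wolf Motor Function Test change would serve.
- State that any claim of a subgroup difference rests on the interaction only.
- Label the subgroup analyses exploratory.
- Remove additional therapy during the training phase from the subgroup list and report its type and amount descriptively by arm.

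The cost is a change of wording and a little programming. The downside is low power, about 41% for a difference in effect of 0.5 at a 50:50 split, so fewer subgroup claims will be possible. The plan should say so, so that a non-significant interaction is not read as proof of a uniform effect.

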### Blinding

Participants are to be enrolled by the respective trial sites' personal.

Participating patients can only be blinded for the comparison of the videotherapy versus the non-video condition, but not for the comparison with the standard rehabilitation. Hence, comparing videotherapy with standard might be biased by the knowledge of the patients to receive a novel treatment. In addition, the intensity of rehabilitation will be comparable between the videotherapy and the non-video group, but not necessarily between both motor exercise groups and the standard group. Therefore, a difference between videotherapy and standard might be caused by a more intense training in the first group. These possible influences will have to be considered in the interpretation of possible study outcomes.

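### One planned subgroup variable, other therapy received during the training phase, is measured after randomisation, so arm comparisons within it are not randomised and can be biased

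*Protocol article*

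**What the plan says.** The section Subgroup analysis, under Outcomes, states: "We will perform pairwise comparisons between all groups (videotherapy, non-video and standard) in dependency of the following variables". The list contains center, age, gender, race, two hemisphere variables and chronicity, and also "type and amount of additional physio- and/or occupational or other therapeutic treatments during training phase". The later Subgroups paragraph under Statistical analysis says only which assessments are used and gives this variable no separate handling.

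The timing is clear from two places. Under Randomization: implementation, allocation takes place "after the respective investigator had screened the respective patient and obtained his/her written informed consent". Table 2 puts screening and the arm-specific instruction visit in week 1, and the training phase in weeks 2 to 7.

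On other therapy, the Interventions section says: "All patients of all groups will conduct their individual rehabilitational programme as prescribed by their respective neurologist". It adds: "The standard rehabilitational programs will not be limited in their amount to allow participation to our study". The Blinding section says that patients can be blinded for videotherapy versus non-video, "but not for the comparison with the standard rehabilitation". It continues: "In addition, the intensity of rehabilitation will be comparable between the videotherapy and the non-video group, but not necessarily between both motor exercise groups". The sentence closes by naming standard care as the arm with which the two exercise arms may not be comparable.

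**The concern.** Randomisation makes the arms comparable on everything fixed before allocation, so a subgroup defined by a baseline variable still gives a randomised comparison. A subgroup defined by something that happens after allocation does not, if the arm can influence it. Patients with a low amount of other therapy may then be a different kind of patient in one arm than in another, and the same holds for those with a high amount.

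Here there are routes by which the arm could influence other therapy. Standard-arm patients know that they receive no trial treatment for six weeks. Patients in the two exercise arms are asked to train 90 minutes per working day. A patient's own recovery during those weeks may also change what is prescribed.

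What is at stake is the reading of this one subgroup. The Blinding section itself notes that a videotherapy versus standard difference might come from more intense training. A table of effects by amount of other therapy could look like a test of that explanation, but comparisons within its strata would not be randomised.

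**Working it through.** **1. Is the variable post-randomisation?** Yes. Allocation follows screening and consent, and the arm must be known by the instruction visit (week 1, days 4-5), which is held only for the videotherapy and non-video groups. The variable is collected over weeks 2 to 7. The primary endpoint is the WMFT change from baseline to after six weeks of treatment, so the two cover the same period.

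**2. Does the protocol fix other therapy so that it cannot differ by arm?** No. It is prescribed by each patient's neurologist and its amount is not limited. The exclusion criterion in Table 1 on other rehabilitation therapies covers only a planned start of interfering therapies, as known at recruitment; it does not fix what is received later.

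**3. The plan's own figures, used for scale.** Sample size: δ = 0.5, α = 0.035 taken as two-sided, power 90%, Mann-Whitney, 20% dropout. Noether's formula with p = Φ(0.5/√2) = 0.638:

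n = (2.108 + 1.282)² / [6 × (0.638 − 0.5)²] = 100.3 per group (unrounded p); 100.3 / 0.80 = 125.4

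The plan states 125, so its figure is reproduced. Since 2.5 points correspond to δ = 0.5, the implied SD of the WMFT change is 2.5 / 0.5 = 5 points.

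**4. Illustration of the bias (assumed inputs, not in the documents).** Suppose there is no treatment effect. The amount of other therapy M has within-arm SD 1 and is lower by s in one arm. M correlates r₁ with an unmeasured recovery potential, the WMFT change correlates r₂ with it, and M is split at its pooled median. With h = s/2, the spurious difference between arms is the same in the high and the low stratum:

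D = 5 × r₁ × r₂ × [φ(h)/(1 − Φ(h)) − φ(h)/Φ(h)]

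The bracket is 0 for s = 0; 0.879 − 0.720 = 0.159 for s = 0.25; 0.964 − 0.646 = 0.318 for s = 0.5; and 1.141 − 0.509 = 0.632 for s = 1.

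| Arm shift s (SD) | r₁ = r₂ = 0.3 | r₁ = 0.3, r₂ = 0.5 | r₁ = r₂ = 0.5 |
|---|---|---|---|
| 0 | 0 | 0 | 0 |
| 0.25 | 0.07 | 0.12 | 0.20 |
| 0.5 | 0.14 | 0.24 | 0.40 |
| 1.0 | 0.28 | 0.47 | 0.79 |

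Entries are WMFT points. Simulation with 2,000,000 patients per setting agrees for the first and third columns (for example 0.78 to 0.79 in the bottom right cell), and there the overall randomised difference stays at 0. If M instead has unit residual variance, with slopes of 0.3 to 0.5 on recovery potential and r₂ = 0.5, shifts of 0.5 to 1.0 SD give about 0.22 to 0.63.

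**5. Direction.** If patients with better potential take more other therapy, the arm that takes less of it looks better in both strata; if they take less, it looks worse in both. The documents do not settle which applies.

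**6. Scale.** The largest entry is 0.79 / 2.5 = 32% of the target difference. With about 100 evaluable patients per arm (125 × 0.80), half in each stratum, the standard error of a stratum difference is about √(25/50 + 25/50) = 1.0 point. Every entry is below one standard error.

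**The case against.** The strongest reply is that the bias is conditional. It needs an arm difference in other therapy and a link between that therapy and prognosis; with either absent it is zero, and the documents report neither. The Interventions section also says that usual programmes are not to be cut back to make room for the trial, which works against DVD time displacing other therapy. This stands: a reader might infer that these subgroup results are certain to be biased, and the documents do not support that. They show only that nothing prevents it.

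The arms are also not equally exposed. Videotherapy and non-video use equivalent material apart from the slideshows, patients can be blinded between them, and the protocol expects comparable intensity. Knowledge of allocation and training burden separate the exercise arms from standard, not from each other. Different recovery could still lead to different therapy in the two exercise arms, but that is the weaker case.

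The magnitudes rest on invented inputs, including the median split, since the protocol names no cut. They are also small against the sampling error of a half-sample stratum. Both points stand. A small bias does not turn the comparison into a randomised one, however. Agreement between strata would not be reassuring either, because both can move the same way.

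Finally, the analysis lies outside the confirmatory testing sequence. That limits the consequence but is no cure: exploratory status bears on error rates, not on selection.

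**Conclusion.** The point holds for this single subgroup variable. As written, the plan compares arms within groups defined by something measured after randomisation that can depend on the arm, chiefly for comparisons with the standard arm. If it does depend on the arm and is related to recovery, the within-subgroup differences are biased even under no treatment effect, and both strata can be biased alike. The size cannot be derived from the documents. It is 0 to about 0.8 WMFT points under SD 5, an arm shift of 0 to 1 SD, correlations of 0.3 to 0.5 and a median split.

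A reader might infer that the trial's main result is compromised, or that the protocol relies on this subgroup to explain that result. Neither is supported. The primary intention-to-treat comparison, the sample size and the other listed subgroups do not condition on this variable, and no section gives the subgroup that explanatory role. This is a limited, easily corrected flaw in one exploratory analysis.

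**What to change.** Delete this variable from the list in the Subgroup analysis section. Report type and amount of other therapy during training descriptively per arm, beside the videotherapy versus standard result. Label any analysis by therapy received as non-randomised, and do not present it as a treatment effect in a subgroup.

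If a subgroup is still wanted, define it by the outpatient therapy planned for after discharge, recorded before randomisation. The prescription current at screening is a doubtful substitute: under Table 1, hospitalised patients are within seven days of discharge from rehabilitation, so it may describe inpatient therapy that is about to end.

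The cost is a change of wording and, if the replacement is used, one extra item at the existing screening visit. One exploratory subgroup analysis is lost or downgraded. No treatment, endpoint, visit or sample size changes.
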